### Randomization

Ultimately, 180 participants will be randomized to the acupuncture treatment plus usual care group or usual care alone group and divided into four centers (see Figure 1). Each center will recruit a total of 45 participants, with 30 assigned to the acupuncture plus usual care group and 15 to the usual care alone group. A block size of 3 is used to assign 2 for acupuncture treatment plus usual care group and 1 for usual care alone group. Separate randomization table will be provided for each center.

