### Study outcome

The primary outcome measure is the hot flush score, produced by multiplying severity and frequency of hot flushes during a 24-hour period in a daily diary, which demonstrates validity and reliability in measuring hot flush activities [27]. Participants will be asked to record the number and severity of daily hot flushes during the entirety of the study period. Participants in both groups will also be routinely encouraged to fill out the diary by periodic short message service (SMS) and phone-call reminder both in order to avoid the selective loss to follow up, that is, selection bias and to prevent the indolence of writing daily diaries which are associated with participant knowledge-related bias in this unblinded trial. We will employ the slightly modified severity rating scale (0:none, 1:mild, 2:moderate, 3:severe, 4:very severe) suggested in the studies of Sloan et al. [27].

We will examine the reduction in hot flushes over a 24-hour period, as well as daytime and nighttime separately for sub-analytic purpose to check whether acupuncture has different effects on daytime versus nighttime hot flushes.

The secondary outcome measure is the Menopause Rating Scale (MRS) to assess other vasomotor symptoms. MRS is a highly qualified self-administered questionnaire for assessment of menopausal symptoms [37]. It contains 11 questions divided into 3 categories: psychological, somatic and urogenital.

We will also estimate the expectations of participants by using the credibility and expectancy questionnaire, aiming to determine whether expectations make a difference to outcome [38,39]. In order to assess expectations without potential influences by participants' knowledge of allocation results, a questionnaire will be administered to eligible women before notification of assignments. Data collection schedule is detailed in table 2.

**Table 2 T2:** Data Collection Schedule

Measures	Screening	Baseline Randomization				End		Follow-up
Week number	-1	0	1	2	3	4	6	8

Sociodemographic characteristics	O							
Hot flush diary	O	O	O	O	O	O	O	O
Credibility and Expectancy questionnaire		O						
MRS		O		O		O	O	O
Medical history	O							
Physical activity	O							
Smoking/Alcohol	O							
Pharmaceutical therapies (OTC and prescribed drugs)	O	O	O	O	O	O		O
Herb medications	O	O	O	O	O	O		O
Adverse effects			O	O	O	O		
FSH, Estradiol	O							
TSH, Free T4	O							

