In case of an unblinded trial, the rater(or assessor) knowledge of treatment assignment could modify the outcome assessment [40]. We employed only patient- reported and self-administered outcomes with concerns of potential rater bias in outcome assessment. However, related bias due to the unblindness might still occur despite all of efforts to prevent them. It should be recognized as an unavoidable limitation of this study design.

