### Statistical methods and sample size

Analyses will be performed for two populations: 1) an intention-to-treat population consisting of all randomized participants with at least one measurable outcome report following acupuncture treatment (missing data will be replaced with last observation values); 2) a per protocol population including only participants without major protocol deviations. All data will be analyzed descriptively. All main analyses will be based on the intention-to-treat population. For primary and secondary outcome measures, the mean differences from baseline values to the end of treatment will be compared using two-sample t-test or Wilcoxon rank sum test. A trend test will also be performed using repeated measures analysis of variance. We adjusted for possible confounders using criteria of statistical significance.

All adverse events reported during the study will be included in the charts; then incidences of adverse events will be calculated. The percentage of the subjects with adverse events in each group will be calculated and compared with the chi-squared test or Fisher's exact test value.

Statistical analyses will be performed using the SAS statistical package program (ver. 9.1.3) and the level of significance will be established at α < 0.05. In calculating the sample size, we assumed a power of 90% and α value of 5%, in order to detect a hot flush score difference of 15.34 with a standard deviation of 26.5 drawn by two previous studies in Korea [24,41]. Therefore the acupuncture plus usual care and usual care alone group (2:1 allocation) will include 120 and 60 participants, respectively, allowing for a 20% withdrawal rate. This implies a sample size of 45 for each center, with 30 participants per acupuncture treatment plus usual care group and 15 per usual care alone group.

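### A single fixed block of 3 (2:1) within each centre of an open trial would let a recruiter who knows the block size deduce about 44% of allocations in advance

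*Protocol article*

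**What the plan says.** The Randomization section of the protocol article fixes the scheme: "A block size of 3 is used to assign 2 for acupuncture treatment plus usual care group and 1 for usual care alone group". It adds: "Separate randomization table will be provided for each center". The planned total is 180, and the quota in every centre is 45 women, split 30 to acupuncture and 15 to the comparison arm. A quota of 45 is exactly 15 blocks of 3. The section mentions no variation in block size and no withholding of it.

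The Study outcome section describes its diary reminders as partly a guard against "participant knowledge-related bias in this unblinded trial". On assessment it says: "We employed only patient- reported and self-administered outcomes with concerns of potential rater bias in outcome assessment". The Interventions section says that the acupuncture is given by doctors belonging to each centre, so a centre can see which of its participants were assigned to it.

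**The concern.** In a 2:1 block of 3, once the single usual-care slot is used, the rest of the block must be acupuncture. After two acupuncture assignments the next must be usual care. In an open trial the earlier assignments are visible, so the next one can often be worked out without any access to the list. Sealed envelopes or telephone release hide the next line but do not prevent that deduction.

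A recruiter who can predict the assignment can time, defer or decline an enrolment according to the woman in front of them. The arms could then differ at entry in traits that affect self-reported hot flushes. The bias measures in the Study outcome section (reminders, self-administered outcomes, and an expectancy questionnaire before notification) address reporting, rater and expectation bias. None of them addresses prediction of the next allocation.

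**Working it through.** **Inputs.** From Randomization: block of 2 acupuncture (A) and 1 usual care (C), four centres, 45 women per centre (30/15), 180 in total. From Statistical methods and sample size: "hot flush score difference of 15.34 with a standard deviation of 26.5", 90% power, 5% alpha, 2:1 allocation, 20% withdrawal. Sidedness is not stated; two-sided is assumed.

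**The plan's own figure.** Usual-care n = (1 + 1/2) × (1.960 + 1.282)² × 26.5² / 15.34² = 1.5 × 10.507 × 702.25 / 235.32 = 47.04, rounded up to 48. Acupuncture is then 96 and the total 144. Dividing by 0.8 gives 60 + 120 = 180, as stated. The sample size is sound; the issue is only the order of assignment.

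**Certain allocations in a block of 3.** The three orders are equally likely. An allocation counts as certain when the earlier ones in its block leave only one arm possible.

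| Order | Certain allocations | Of which A | Of which C |
|---|---|---|---|
| CAA | 2 | 2 | 0 |
| ACA | 1 | 1 | 0 |
| AAC | 1 | 0 | 1 |
| Sum over 9 slots | 4 | 3 | 1 |

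- Share certain: 4/9 = 44.4%, or 20 of 45 per centre and 80 of 180 overall, in expectation.
- Split: 3/9 × 180 = 60 certain acupuncture (half of 120) and 1/9 × 180 = 20 certain usual care (one third of 60).
- By position: the first is never certain, the second is certain one time in three, and the third always.

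**Best-guess accuracy.** First position: 2/3. Second: (1/3 × 1) + (2/3 × 1/2) = 2/3. Third: 1. The mean is (2/3 + 2/3 + 1)/3 = 7/9 = 77.8%. Always guessing acupuncture gives 66.7%.

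**Other block sizes.** For a block with *a* acupuncture and *b* usual care, the expected number of certain allocations is a/(b+1) + b/(a+1).

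| Fixed block | Expected certain | Share | Best guess |
|---|---|---|---|
| 3 (2+1) | 2/2 + 1/3 = 1.333 | 44.4% | 77.8% |
| 6 (4+2) | 4/3 + 2/5 = 1.733 | 28.9% | 74.4% |
| 9 (6+3) | 6/4 + 3/7 = 1.929 | 21.4% | 72.8% |

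For blocks of 3, 6 and 9 chosen at random with equal probability, a simulation of 45-woman centre lists was run. The recruiter was assumed to know the set of sizes and to track the sequence perfectly. About 3.6% of allocations were certain and best-guess accuracy was about 74%.

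**Effect of the change on balance and power.** If a list is cut at 45 inside a block of 9, the largest departure from 2:1 is two women. For example, three C first is 3 where 1 is expected, and six A first is 6 where 4 is expected. In the simulation about 78% of lists ended at exactly 30/15 and nearly all the rest were one woman off. If all four centres were one off in the same unfavourable direction, the split would be 124/56, or 99.2/44.8 after 20% withdrawal. Power (normal approximation) is then Φ(15.34 / (26.5 × √(1/99.2 + 1/44.8)) − 1.960) = Φ(1.256) = 89.5%, against 90.6% for 96/48.

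**The case against.** Several parts of the case for leaving this alone have force.

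- **The 44% is conditional.** It needs a recruiter who knows the block size and follows the centre's sequence. The article does not say that recruiting staff are told the size. A reader might infer that 44% of allocations are simply known in advance; the document supports only that they could be deduced under those conditions. Both conditions are plausible with one constant size, four centres and open treatment.
- **The tables may not be at the centres.** A reader might infer from "Separate randomization table will be provided for each center" that staff are handed the list. The sentence reads equally well as one list per centre, that is, stratification. Who holds the lists and how assignments are released are details that an article commonly leaves to the full protocol. The point does not depend on them.
- **The information gain is smaller than 44% sounds.** Three quarters of the certain allocations (60 of 80) are acupuncture, already 67% likely under 2:1. Best-guess accuracy rises by 11 percentage points, and varying the block size takes back only about 4 of these. That is correct. The larger gain from varying the size is in certainty, from 44% to about 4%.
- **Some steering could be seen and adjusted for.** A reader might conclude that no analysis could repair the bias. That goes too far. The hot flush diary starts at screening, the outcome is change from baseline, expectancy is measured before notification, and the statistical section provides for confounder adjustment. What stands is that selection on traits nobody records cannot be adjusted for.
- **Room and motive are limited.** Entry rests on a diary threshold, laboratory tests and listed exclusions, and usual-care women may have acupuncture after four weeks. This narrows the scope for steering but does not remove the option to defer or decline an enrolment.

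**Conclusion.** The concern holds as a risk created by a rule that the article states. A single fixed block of 3, the smallest possible at 2:1 and the most predictable of the sizes compared, is used within each centre of an unblinded trial. On average 4/9 of allocations (about 80 of 180) could be deduced beforehand, about 60 acupuncture and 20 usual care. Best-guess accuracy would be 78% against 67%. These figures assume complete blocks and a recruiter who knows the size and tracks assignments.

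The documents do not show that enrolment was steered, and they give no basis for the size of any resulting bias in the hot flush score difference. Predictability is quantified here; its effect on the result is not. The group sizes and the sample size calculation are internally consistent and unaffected.

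**What to change.** Within each centre, replace the fixed block of 3 with 2:1 blocks of randomly varying size, for example 3, 6 and 9. Withhold the sizes from recruiting staff, and from any public document, until enrolment closes. If the full protocol does not already provide for it, release each assignment only after the woman's enrolment is confirmed.

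The cost is four regenerated lists. A centre may finish one woman, at most two, away from exactly 30/15, with negligible effect on power.

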**Figure 1 F1:**
[figure not shown]
Flow diagram of study design.

### Ethics

Oral and written consent will be obtained from each participant. This study was approved by the institutional review boards at the Dongguk International Hospital, East-West Neo Medical Center of Kyung Hee University, Semyung University Hospital and Dong Eui Medical Center.

### Statistical methods and sample size

Analyses will be performed for two populations: 1) an intention-to-treat population consisting of all randomized participants with at least one measurable outcome report following acupuncture treatment (missing data will be replaced with last observation values); 2) a per protocol population including only participants without major protocol deviations. All data will be analyzed descriptively. All main analyses will be based on the intention-to-treat population. For primary and secondary outcome measures, the mean differences from baseline values to the end of treatment will be compared using two-sample t-test or Wilcoxon rank sum test. A trend test will also be performed using repeated measures analysis of variance. We adjusted for possible confounders using criteria of statistical significance.

All adverse events reported during the study will be included in the charts; then incidences of adverse events will be calculated. The percentage of the subjects with adverse events in each group will be calculated and compared with the chi-squared test or Fisher's exact test value.

Statistical analyses will be performed using the SAS statistical package program (ver. 9.1.3) and the level of significance will be established at α < 0.05. In calculating the sample size, we assumed a power of 90% and α value of 5%, in order to detect a hot flush score difference of 15.34 with a standard deviation of 26.5 drawn by two previous studies in Korea [24,41]. Therefore the acupuncture plus usual care and usual care alone group (2:1 allocation) will include 120 and 60 participants, respectively, allowing for a 20% withdrawal rate. This implies a sample size of 45 for each center, with 30 participants per acupuncture treatment plus usual care group and 15 per usual care alone group.

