### Interventions

TKA regimens designed according to TKM clinical experts will be used in this trial for alleviating hot flushes and vasomotor symptoms by balancing yin and yang in the participant. These regimens were also used in two previous studies [25], one of which is unpublished and mentioned above. The TKM doctors who conduct the treatments have practiced for at least 3 years in the clinic; they belong to each clinical center spread among different provinces in South Korea.

Participants will be randomly assigned to either the acupuncture treatment plus usual care group or the usual care alone group. The acupuncture treatment plus usual care group will receive acupuncture 3 times/week, for a total of 12 sessions. Six acupuncture points (ST36, SP6, LI4, PC6, HT7, HT8) will be inserted bilaterally in the four peripheral extremes and one point (CV4) will be inserted unilaterally in the lower abdominal region. TKM doctors will manually manipulate the acupuncture needles with de-qi sensation and maintain the needles for 20 minutes with intermittent manual stimulation. Infrared irradiation will be used to warm the lower abdomen during the 20 minutes of acupuncture treatment, as it is performed in conjunction with acupuncture, generally.

TKM doctors will use sterile, disposable needles with a length of 40 mm and a diameter of 0.25 mm (Dongbang Acupuncture Inc, Korea). They will be inserted to a depth of 3–15 mm, according to the points selected.

Participants who will be allocated to usual care alone group will receive no acupuncture treatments throughout the 4 weeks. They will record their hot flush symptoms in a daily diary. After four weeks, if participants elect to try the acupuncture treatment, the same treatment will be provided.

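### The intention-to-treat set requires an outcome report after acupuncture, so entry depends on a post-randomisation event that differs by arm

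*Protocol article*

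**What the plan says.** The section Statistical methods and sample size names two populations. The first, called intention-to-treat, is "all randomized participants with at least one measurable outcome report following acupuncture treatment", with the rule that "missing data will be replaced with last observation values". The same paragraph states: "All main analyses will be based on the intention-to-treat population". For the primary and secondary outcomes, "the mean differences from baseline values to the end of treatment will be compared using two-sample t-test or Wilcoxon rank sum test". Table 2 places the end of treatment at week 4.

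The Interventions section says of the control arm: "Participants who will be allocated to usual care alone group will receive no acupuncture treatments throughout the 4 weeks". It adds: "They will record their hot flush symptoms in a daily diary". It then opens the treatment to controls: "After four weeks, if participants elect to try the acupuncture treatment, the same treatment will be provided". Table 2 continues the diary to weeks 6 and 8, and the abstract names week 4 and/or week 8 for the primary endpoint. No other part of the article gives a separate entry rule for controls.

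**The concern.** The main analysis set should preserve the comparison that randomisation created. Here the entry condition is tied to a treatment that one arm does not receive during the comparison period. The condition therefore either cannot be applied to controls as written, or is applied to one arm only.

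This is a rule the article states, not a detail it leaves to a fuller document. An analyst who has to apply it must choose among several readings, and they select different women. The trial is unblinded, and the Study outcome section itself worries about selective loss to follow-up, so that choice should be settled before any outcome data are seen. Every main analysis uses this set.

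**Working it through.** **The plan's own figure.** Inputs from Statistical methods and sample size: difference 15.34, SD 26.5, power 90%, α 5% (taken as two-sided), allocation 2:1, withdrawal 20%.

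- Controls before withdrawal: (1 + 1/2) × [26.5 × (1.960 + 1.282) / 15.34]² = 47.04, rounded up to 48. Acupuncture: 2 × 48 = 96.
- After withdrawal: 48 / 0.8 = 60 and 96 / 0.8 = 120.

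This reproduces the stated 60 and 120. The calculation presupposes that controls are analysed as a full arm, so the plan plainly expects them in the main set.

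**Applying the entry condition to each arm.** The possible readings are:

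1. *Literal: a report after the woman has had acupuncture.* Up to week 4, controls "will receive no acupuncture treatments throughout the 4 weeks", so no control report by then can meet the condition. Membership is decided per woman, however, not per visit. A control who elects acupuncture after week 4 and then completes a week 6 or week 8 diary would qualify, and her week-4 data would then be analysed. The number of controls in the set is therefore the number who elect acupuncture and then report, anywhere from 0 to 60. Under this reading, the control group consists only of women who crossed over.

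2. *Lenient: the acupuncture condition applies to the acupuncture arm, and controls need only some post-baseline report.* Two groups must be kept apart:
   - Women who leave before any post-baseline report are dropped in both arms, so the rule is the same for each.
   - Women randomised to acupuncture who are never needled but still keep the diary are dropped. A control with the same diary is kept. This exclusion has no counterpart.

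3. *After the treatment period, in both arms.* Anyone who stops reporting before the end of treatment is dropped. The last-observation rule in the same sentence would then have little to fill at week 4, so this reading sits badly with the text.

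**Illustration for reading 2.** The document gives no rate of never-treated women, so the fraction p is an assumption. Suppose p of the acupuncture arm is dropped this way, those women would have changed on average as controls did, and the analysed set shows the planning difference D = 15.34. The all-randomised difference is then (1 − p) × D, and the ratio of the two is 1 / (1 − p).

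| p (assumed) | Women of 120 | (1 − p) × 15.34 | Overstatement |
|---|---|---|---|
| 1% | 1.2 | 15.19 | about 1% |
| 5% | 6 | 14.57 | about 5% |
| 10% | 12 | 13.81 | about 11% |

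**After the fix.** If the set is all randomised women as allocated, the sizes stay at 60 and 120. By normal approximation, power is Φ(15.34 / [26.5 × √(1/60 + 1/120)] − 1.96) = 95.6% with no loss, and 90.6% with 48 and 96 women.

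**The case against.** The strongest reply is that the literal reading is obviously not intended. The plan compares two groups, sizes them at 120 and 60, has controls keep a daily diary, and prompts both groups by text message and telephone. The phrase was probably meant as a report after randomisation or baseline, and requiring one post-baseline report is a common modified intention-to-treat convention. This stands as an account of intent. It does not repair the rule, because the article nowhere says so and gives controls no other condition.

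Three stronger readings are tempting and are not supported:

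- A reader might infer that the set contains no controls at all. That holds only for reports up to week 4; controls who take up acupuncture later and then report would literally qualify.
- A reader might infer that all early leavers are excluded from the acupuncture arm alone. A control with no post-baseline report has no measurable outcome either and is dropped by the same clause. Only the never-needled women who still report are excluded one-sidedly. Treatment is given three times a week and diaries are daily, so a woman who starts treatment would normally have a qualifying report within days, and this group may be small.
- A reader might infer that the rule demonstrably favours acupuncture, by 11% for example. That direction and size follow only if the dropped women gain nothing, and the 11% also needs 10% of one arm to fall in this group. The planned 20% is overall withdrawal and says nothing about how many women are never treated.

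**Conclusion.** The point holds. As written, the entry rule for the set used in all main analyses does not fit the control arm, and neither the literal nor the lenient reading treats the arms alike. Literally, controls enter only by choosing acupuncture after week 4. Leniently, untreated women who keep reporting are lost from the acupuncture arm only. The label intention-to-treat is not earned in either case.

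The existence of the defect follows from the article's text and needs no assumption. Its effect on the estimate cannot be determined from the document. The range of about 1% to 11% is conditional on an assumed 1% to 10% of the acupuncture arm being dropped with zero benefit. If those women improved more or less than assumed, the size would change and the direction could too. The sample size calculation is sound and is not affected.

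**What to change.** Define the main set as all randomised participants, analysed in the arm to which they were assigned, regardless of treatment received. If a data condition is kept, replace the reference to acupuncture with at least one diary record after randomisation, in identical words for both arms, and call the result a modified intention-to-treat set. Diaries are already scheduled for all participants in Table 2, so no new data collection is needed.

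The cost is a wording change made before outcome data are examined, and possibly a slightly less favourable estimate. With all randomised women included, those without any post-baseline diary need a stated handling rule. Whether the last-observation rule should give way to a longitudinal model or multiple imputation is a separate question that this correction does not decide. The planned 120 and 60 stay as they are.

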## Background

Hot flushes are the most frequent climacteric symptom and a major cause of suffering in menopausal women [1,2]. Diminished overall quality of life, social distress and emotional embarrassment are also frequent complaints due to menopause-associated hot flushes [3].

The prevalence of hot flushes varies according to ethnicity, region and cultural characteristics [4,5]. Most women experience hot flushes for 6 months to 2 years [4]. For many women, most menopause-related vasomotor symptoms including hot flushes tend to resolve spontaneously within a few months [6]. About 29% of 60-year-old women, however, report persistent hot flushes [6].

It is well known that the most effective treatment for hot flushes is hormone replacement therapy (HRT) [7]. Recent research performed by the Women's Health Initiative and the Million Women Study, however, suggests HRT may increase the risk of coronary heart disease [8], stroke [9], breast and endometrial cancer [10,11]. These findings regarding the adverse effects and potential risks of HRT have led to an expanded interest in non-hormonal therapies for managing hot flushes [12]. However, there are only limited data to support their use, and some adverse effects may be linked to certain types of non-hormonal therapies [13]. Herbs and phyto-estrogens have also been used in the clinic to alleviate menopausal symptoms, and many individual trials reported positive results for these therapies in reducing hot flushes. Such methodologies still require further research in terms of efficacy and long-term safety [14,15].

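### The main analysis carries last observations forward although scores are expected to fall, so withdrawal can bias the week-4 difference in either direction

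*Protocol article*

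**What the plan says.** In the protocol article, under Statistical methods and sample size, the intention-to-treat population is limited to randomised women with at least one outcome report after treatment, and in it "missing data will be replaced with last observation values". The section continues: "All main analyses will be based on the intention-to-treat population". For the primary and secondary outcomes, "the mean differences from baseline values to the end of treatment will be compared using two-sample t-test or Wilcoxon rank sum test". The sample size is set to "detect a hot flush score difference of 15.34 with a standard deviation of 26.5" at 90% power and 5% significance, giving 120 and 60 women, "allowing for a 20% withdrawal rate".

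The Background says that for many women "most menopause-related vasomotor symptoms including hot flushes tend to resolve spontaneously within a few months", and it reports that many acupuncture studies saw within-group falls of at least half. The section Study outcome describes a self-completed daily diary in an unblinded trial and names selective loss to follow-up as a risk. Its stated remedy is text-message and telephone reminders to both arms. The article gives no other rule for missing values and no sensitivity analysis to this one. The repeated-measures analysis of variance is described as an added trend test, not as another way to handle missing data.

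**The concern.** Carrying the last value forward gives the right week-4 mean only if scores stop changing when a woman leaves. The article's own account is that they fall, without treatment and with it. Entry on a high score in the week before screening adds some regression to the mean.

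Each woman who leaves is therefore credited with only part of the change she would have shown by week 4. The missing parts cancel between arms only if the arms have the same fall and the same withdrawal. Otherwise the estimated difference is shifted, and neither the t-test nor the rank-sum test reflects that shift. This concerns the primary estimate, and the article itself fixes the rule; it is not a detail left to an analysis plan.

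**Working it through.** **Step 1: the plan's own figure.** With difference 15.34, SD 26.5, two-sided 5%, 90% power and 2:1 allocation, the control arm needs (1 + 1/2) × (1.960 + 1.282)² × 26.5² / 15.34² = 47.0, so 48 controls and 96 in the acupuncture arm. Dividing by 0.80 gives 60 and 120. The stated size reproduces and is not in question.

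**Step 2: formula.** Let *d* be the proportion leaving an arm and *f* the average share of the week-4 change reached at the last diary entry. Then

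carried-forward mean change = true change × [1 − *d*(1 − *f*)].

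The article gives neither *d* by arm nor *f*. With a linear fall and exit spread evenly over weeks 1 to 3, *f* = 0.50; the range 0.25 to 0.75 covers exit after week 1 to exit after week 3.

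**Step 3: true difference 15.34, 20% withdrawal in each arm.**
- *f* = 0.25: 15.34 × 0.85 = 13.04
- *f* = 0.50: 15.34 × 0.90 = 13.81
- *f* = 0.75: 15.34 × 0.95 = 14.57

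The size of the control fall does not matter here, because both arms are scaled alike.

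**Step 4: no true effect, both arms fall by 10 points, *f* = 0.50.** The false difference is 10 × (difference in *d*) × 0.50.
- 10% v 30%: 9.5 − 8.5 = 1.0
- 10% v 40%: 9.5 − 8.0 = 1.5
- equal withdrawal: 0

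The arm with more withdrawal looks worse, so the sign depends on which arm that is. With 10% in acupuncture and 40% in control, overall withdrawal is (12 + 24)/180 = 20%, the planned total.

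**Step 5: true difference 15.34, unequal withdrawal, *f* = 0.50.**

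| Control fall | Withdrawal, acupuncture / control | Estimate |
|---|---|---|
| 5 | 10% / 40% | 20.34 × 0.95 − 5 × 0.80 = 15.32 |
| 10 | 10% / 40% | 25.34 × 0.95 − 10 × 0.80 = 16.07 |
| 5 | 40% / 10% | 20.34 × 0.80 − 5 × 0.95 = 11.52 |
| 10 | 40% / 10% | 25.34 × 0.80 − 10 × 0.95 = 10.77 |

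Over control falls of 0 to 10 and *f* from 0.25 to 0.75, the bias runs from −6.85 to +1.10. The negative extreme needs 40%/10%, which is (48 + 6)/180 = 30% overall, above the planned 20%.

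**Step 6: simulation.** Each scenario had 3,000 trials of 120 and 60 women, a linear fall, an SD of 26.5 for the week-4 change, and exit either unrelated to scores or related to the week-1 score. With a true 15.34, the likelihood-based week-4 estimate averaged 15.25 to 15.51 in every scenario. Coverage of the nominal 95% interval after carry-forward was about 93 to 95% at 20%/20% and 80 to 85% at 40%/10%. With no effect, rejection was 4.5 to 7.7%.

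**Step 7: precision.** At 20%/20% with a true effect, the mean reported t-test SE after carry-forward was 4.09 to 4.33, and the estimator's actual sampling SD was 4.12 to 4.20. The two agree.

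**The case against.** **The standard error.** A reader might infer that carry-forward makes the standard error too small, since 26.5 × √(1/120 + 1/60) = 4.19 while the 96 and 48 women actually observed would give 26.5 × √(1/96 + 1/48) = 4.68, about 11% more. That compares two different estimators. Step 7 shows that the t-test SE matches the carry-forward estimator's own variability. What stands is narrower: carried values count as full information about week 4, and the interval makes no allowance for the bias.

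**The direction.** A reader might also infer that untreated controls will leave more often and so create a false benefit. The article gives no withdrawal by arm. Controls may have acupuncture after four weeks, which is a reason to stay; the other arm carries the burden of 12 sessions; both arms get reminders. Even with more control withdrawal, a true effect may be estimated almost without bias (15.32 in step 5).

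**The course of scores.** If most of the fall comes early, the bias shrinks. With 80% of it reached by week 1 and the rest linear, *f* averages (0.800 + 0.867 + 0.933)/3 = 0.867. The 1.0 in step 4 then becomes 10 × 0.20 × 0.133 = 0.27, and the 13.81 in step 3 becomes 15.34 × (1 − 0.20 × 0.133) = 14.93. This stands, and it is why the figures are illustrations.

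**The size.** At 20%/20% the harm is modest. An estimate of 13.81 with SE 4.19 still has about 91% power, and false differences of 1.0 and 1.5 raise the type I error only to about 5.7% and 6.5%. Total error at 20%/20% is also no worse than for the likelihood estimate (simulated root mean square error 4.38 to 4.45, against a sampling SD of 4.48 to 4.56). The case for changing is that the bias depends on a withdrawal pattern nobody can know in advance: at 40%/10% the same comparison is 5.56 to 6.37 against 4.44 to 4.73.

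**The replacement.** A mixed model assumes data are missing at random, which withdrawal prompted by knowing one's allocation may violate. The simulation satisfied that assumption by construction. This also stands, and the fix allows for it.

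**Conclusion.** The point holds as a correctable weakness in the primary analysis. The stated rule assumes frozen scores where the article itself expects falling ones. At the planned withdrawal, split equally, a true 15.34 is reduced to about 13.8 (13.0 to 14.6), roughly a 10% loss. Unequal withdrawal of 10% versus 30 to 40%, with a 10-point fall in both arms, produces a false difference of roughly 1 to 1.5 points in either direction. Larger bias needs more withdrawal from the acupuncture arm than the plan allows for. Equal withdrawal with no effect leaves the comparison unbiased. All of this depends on assumed withdrawal by arm, control-arm fall and timing of exit, none of which the article gives. The documents support neither a claim that the bias favours acupuncture nor a claim that the reported standard error is wrong for the estimator used.

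**What to change.** Make the main analysis a likelihood-based repeated-measures model on the weekly mean diary scores for weeks 1 to 4, with terms for arm, week, arm-by-week, baseline score and centre. Take the week-4 contrast between arms as the primary estimate; this is the end-of-treatment comparison that Statistical methods and sample size already names. Every woman with at least one diary week on study contributes what she recorded, and nothing is carried forward. Keep last-observation replacement at most as a sensitivity analysis.

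Add one sensitivity analysis for data not missing at random: shift the imputed week-4 values of women who left by a fixed amount, allowed to differ by arm, and report how large the shift must be to change the conclusion.

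The cost is a change of wording and a little more programming. The daily diaries are already collected, the SAS version already named can fit the model, and no visit or sample-size change is needed, since 96 and 48 observed women already give the planned 90% power. The remaining downside is reliance on missing at random, which the delta-adjusted analysis is there to test.
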